# The efficacy of pivmecillinam: 3 days or 5 days *t.i.d* against community acquired uncomplicated lower urinary tract infections – a randomized, double-blinded, placebo-controlled clinical trial study protocol

**DOI:** 10.1186/s12879-016-2022-0

**Published:** 2016-12-01

**Keywords:** Cystitis, UTI, Pivmecillinam, General practice, Study protocol

## Abstract

**Background:**

Uncomplicated lower urinary tract infections (LUTI) are very common, and presumably around 200,000 female patients are treated for this annually in Denmark. The current Danish national clinical practice guidelines recommend pivmecillinam as a first-line drug (i.e.*,* 400 mg t.i.d. for 3 days). Pivmecillinam is also one of the first-line drugs recommended in the international guidelines for LUTIs (i.e.*,* 400 mg b.i.d. for 5 days). The international recommended duration is based on evidence saying that a 7-day regimen is better than a 3-day regimen. However, no data says that a 5-day regimen is superior to a 3-day regimen. With this study we aim to identify and to compare the efficacy of pivmecillinam 400 mg t.i.d in a 3-day respectively 5-day regimen, against community acquired uncomplicated LUTI, i.e.*,* in women at the age of 18–70 year old.

**Method/design:**

The general practitioner will at consultation give a suitable patient the opportunity to participate in the study. If the patient will give her consent, a double-blinded kit (i.e.*,* the antibiotic with/without placebo, questionnaires and self-urinary samples) will be given to the patient. We aim for 161 evaluable patients in each arm.

**Discussion:**

Pivmecillinam is an excellent choice against urinary tract infections and we believe this study will fill in the gaps and strengthen the evidence on the treatment against one of the most common infections in our society. Thus, aiming to provide a more rational and ecological beneficial antimicrobial therapy.

**Trial registration:**

EudraCTno.: 2014-001321-32.

## Background

Uncomplicated lower urinary tract infections (LUTIs) are very common (i.e. 10% of all women has it each year and 60% of all women experience at least one episode during their lifetime) [1], and we presume there are about 200,000 patients treated for this in Denmark annually. Most patients are otherwise healthy women, and these infections are often the main reason of exposure to antibiotics for these patients [2]. Uncomplicated LUTIs are primarily community acquired and diagnosed as well as treated in primary care. The most common pathogen is *Escherichia coli* [2, 3], and diagnosis can be made clinical with 90% positive predictive value (i.e. new onset dysuria, pollakisuria and urgency, together with absence of vaginal discharge or pain) [4].

In Denmark, the current clinical practice recommendations is pivmecillinam (i.e.*,* 400 mg *t.i.d* for 3 days) as the first line drug against uncomplicated LUTIs [5]. Pivmecillinam is a prodrug of mecillinam. It is an amidinopenicillin, selective and highly effective against Gram-negative bacteria, especially *E. coli.* The side effects are few; most commonly reported are mild gastrointestinal symptoms (e.g. nausea) [6]. It has for a long time primarily been used for UTIs in the Scandinavian countries [7]. Several studies have shown pivmecillinam to be a safe and effective agent in the treatment of LUTIs [6, 8]. Even in countries where it is well used, there seems to be low rates of resistance [3, 8, 9] (e.g. 5% resistance in *E. coli* of the Danish primary sector [10]), and indications of a low rate of collateral damage and low risk of clonal spread of resistance [11].

The current international and European clinical practice guidelines for acute uncomplicated UTI recommend pivmecillinam as one of the first line drugs, the therapy is recommended to be 400 mg *b.i.d* for 5 days. Although, at the same time saying 400 mg *b.i.d* in any duration between 3 and 7 days is an appropriate choice, but pointing out a 5-day or a 7-day course probably is superior to a 3-day course [2]. The recommended duration is, however, based on evidence showing a 7-day course is better than a 3-day course [12]. Clinical studies on pivmecillinam treatment of LUTI caused by ESBL producing bacteria shows different success rates, i.e. 56% (200 mg *t.i.d*.) and 80% (mainly 400 mg *t.i.d*) [13, 14]. The higher success rate of 400 mg is supported by Monte Carlo simulations [15]. Thus, evidence point to a superiority of 400 mg dose.

With this knowledge, we wanted to compare the efficacy of a 400 mg *t.i.d.* 3-day versus 5-day regimen of pivmecillinam against uncomplicated LUTI.

## Methods

### Design

This study will be a prospectively, double-blinded, randomized, multi-center placebo-control trial, comparing the efficacy of a 3- and 5-day regimen of pivmecillinam 400 mg. *t.i.d.* against uncomplicated urinary tract infections. The study will be conducted according to good clinical practice (GCP) and each patient has to sign a consent form to be able to participate.

### Study population

#### Inclusion criteria

Women in the age of 18–70 years old, with clinical features of community acquired uncomplicated LUTI, with the ability to understand the study and give consent, can participate. Patients need to have a symptom cumulative score of ≥2 p (i.e. none, mild, moderate or severe, scoring 0–3, respectively) in accordance to the validated questionnaires for uncomplicated UTI [16]. The following symptoms are included:Dysuria (i.e. pain or burning sensation when urinating)Urgency (i.e. feeling an increased and more frequent need to urinate)Pollakisuria/frequency (i.e. urinating more frequently than usually)

An accepted definition of uncomplicated LUTI is symptoms in concordance with uncomplicated LUTI and significant bacteriuria of uropathogenic bacteria [1], but we choose not to include the latter criteria in our intention to treat (ITT) analysis. This is because we want the included patients in the ITT group to mimic the realistic settings as much as possible (i.e. in which patients with uncomplicated LUTI will receive antibiotic therapy without urine samples in most primary care settings).

#### Key exclusion criteria

Allergy to penicillins and cephalosporines.Clear signs of (i.e. high fever ≥38,5 °C or flank pain/tenderness) or high suspicion of pyelonephritis.Any condition that may lead or predispose to complicated urinary infection (i.e. indwelling urinary catheter, pregnancy, immunosuppressive therapy, abnormal urinary tracts, recurrent UTI, serious neurological disease affecting the bladder).Porphyria or systemic primary carnitine deficiency or of the type organic aciduria (i.e. methylmalonic aciduria and propionacid anemia).Symptoms correlating with differential diagnosis (i.e. vaginal discharge or pain).Ongoing/current antibiotic therapy.Oesophageal stricture.Current intake of allopurinol (i.e. increases the risk of allergic skin reaction to mecillinam) or probenecid (i.e. decrease the renal excretion of mecillinam) or valproate.Currently part of another clinical trial. Inability/unable to understand and/or take part in the clinical trial

#### Settings and recruitment

The patients will be recruited in general practice (GP) clinics by GPs in Denmark. With nine collaborating clinics we aim to recruit 161 evaluable patients in each arm over app. 24 months. Female patients will, during this period, be screened for uncomplicated LUTI and recruited to the study. To receive the treatment goal as soon as possible the investigators will contact and support the GPs from time to time during the trial period.

#### Intervention

All patients included will receive pivmecillinam therapy for 3 days or 5 days. The 3-day regimen group will receive blinded placebo tablets on day 4 and 5. If a secondary antibiotic treatment is required due to treatment failure (i.e. ongoing or worsening symptoms), a new antibiotic cure will be chosen in line with the results from the pre-treatment (inclusion day) urine culture. The GPs will be at any time welcome to call the Department of Clinical Microbiology (DCM) (i.e. central investigation site) for consultation in the matter.

##### Drug processes and randomization

All drug process will be conducted according to the requirements of Good Manufacturing Practice (GMP) and Good Distribution Practice (GDP), in accordance with the Danish Health and Medicine Authority. The placebo tablets will be indistinguishable from the pivmecillinam tablets (i.e. in color, taste and design), and packaged in an identical blister-packaged (i.e. the commercial pivmecillinam blister-package). To guarantee blinding of both the patients, treating physicians and the investigators, a central randomization will be conducted by an independent qualified researcher. The randomization will be conducted in R 3.2.2 [17], with each kit given a number from 1 to 500 and randomized into 25 blocks including 20 kits each. The kits will be delivered to the collaborating clinics. Encrypted data will be stored centrally at the hospital research department and the collaborating hospital pharmacy for possible de-blinding.

#### Questionnaires

The GP will receive an inclusion-questionnaire that he/she will fill out on day 0 (inclusion day). The questionnaires his will include age, positive inclusion criteria (i.e. LUTI symptom load), exclusion criteria, debut date of symptoms, and annual incidence of LUTI. All participants will be given a diary-questionnaire for day 0 to day 7*.* In which they daily will answer questions on LUTI symptoms, score them of severity on daily bases and report on which day they feel completely cured (i.e. back to habitual conditions). They will also be asked to register impairment in daily life activities and quality (i.e. work, physical activity, sleep, mental well-being) similar to the symptom score, previous UTI, travel, weight (i.e. >70 kg) possible adverse effects, adherence to the therapy, use of analgesics and other optional information. The patient will also receive a second follow-up questionnaire which need to be filled out once anytime around day-28 (i.e. possible symptoms or side effects since end of therapy, current status of questions asked in the symptom-diary). All questionnaires on symptoms are constructed according to the validated questionnaires for LUTI symptom score [16]. They will be submitted together with the urine samples. All of the patients’ questionnaires will be so patients can easily understand and answer the questions.

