#### Microbiological diagnostics

One pre-treatment urine sample (day 0) with optional urine-dipstick, and two control urine samples (day 8–10 and day 28–30, respectively) will be sampled from the patient. The three urine samples will be sent to the DCM, Hvidovre University Hospital, Denmark, for examination of the presence and count of uropathogenic bacteria. In presence of significant bacteriuria (i.e. ≥10^3^ bacteria/ml [*E. coli*] / ≥10^4^ bacteria/ml [other uropathogenic bacteria]) the isolates will also be examined for resistance mechanisms and patterns, minimal inhibitory concentration (MIC) to mecillinam (i.e. by E test, AB Biodisk, bioMe’rieux, Marcy-l’E’ toile, France) and determining the bacterial specimen (i.e. MALDI-TOF, Brukner, Germany). All urine samples will processed according to laboratory routine and susceptibility tested according to EUCAST guidelines [18]. During the study all significant uropathogenic isolates will be stored at minus 80 °C. At the end of the study these isolates will be genetically examined to determine their more specific identity/type, i.e. so we can evaluate if the potential relapse is either a true relapse or a reinfection (i.e. the same or different type of bacterial specimen).

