### Follow-up

The investigators at the central laboratory will be calling or sending text messages (patient’s decision) to the included patients to follow-up on the questionnaires and control urine-samples, as well as answering any questions the patients might have. The phone calls or text-messages are app. made on day 3–5, day 9–11 and day 28–30, respectively. However, not at any time will we try to increase the adherence to the treatment, since the study ought to be mirroring a realistic patient situation.

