## Outcome

### Primary endpoint

We have two co-primary endpoints:
**Co-primary endpoint no. 1** –clinical efficacy (i.e. which group will be clinically cured fastest and proportion of patients cured at day four).
**Co-primary endpoint no. 2** – bacteriological efficacy (i.e. proportion of patients bacteriologically cured at first control urine sample).

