### Procedures to evaluate endpoints

By comparing the questionnaires we can evaluate the clinical endpoints. By examining the urine samples we can evaluate the bacteriological endpoints. By asking for a questionnaire on day 28 we can evaluate any relapse/reinfection, hospitalization or secondary consultation, and afterwards look in the collaborating department of clinical microbiology’s databases for urosepsis or pyelonephritis.

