## Power, sample size and analysis

### Definitions

The intention-to-treat (ITT) analysis will be consisting of all included patients (i.e. patients that present with symptoms of uncomplicated LUTI and are included in the study). The per-protocol (PP) analysis will be consisting of all the patients that follow-up with clinical and bacteriological data (i.e. excluding the dropouts). The need-to-treat (NTT) analysis will be stratified from the PP analysis to only include patient with true uncomplicated LUTI (i.e. symptoms and significant bacteriuria, only isolates susceptible to mecillinam).

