### Power analyze

We hypothesize that there is a 15% absolute differences in efficacy between the groups, measured in clinical efficacy. We believe there to be an even bigger difference in bacteriological efficacy. Assuming an efficacy of 90 and 75% for 5 days and 3 days therapy, respectively, using a double-sided test with *p* < 0.05, and a statistical power of 0.8, we will need 113 patients in each group for the NTT analysis. With an estimated fall-out rate of app. 30% between each arm; 161 patients per group will need to be included for the PP analysis, and 230 in each group for the ITT analysis. There is a possibility for an interim analysis after 300 included participants, since we cannot reject a possibility for a higher (i.e. 20%) absolute efficacy.

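### The day-4 clinical endpoint is tied to urine delivery, firmly in the PP definition and probably in ITT through the diary's return route

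*Protocol article*

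**What the plan says.** - **Source of the score.** Questionnaires: "All participants will be given a diary-questionnaire for day 0 to day 7". Procedures to evaluate endpoints: "By comparing the questionnaires we can evaluate the clinical endpoints".
- **Endpoint.** Primary endpoint describes clinical efficacy as "which group will be clinically cured fastest and proportion of patients cured at day four". Clinical cure is a cumulative symptom score below 2, so no urine result enters it. The Outcomes paragraph of the Discussion names clinical effect as the main focus.
- **Return route.** Questionnaires: "They will be submitted together with the urine samples". No other route is described.
- **Urine dates.** Microbiological diagnostics: "two control urine samples (day 8–10 and day 28–30, respectively) will be sampled from the patient". The Outcomes paragraph of the Discussion instead puts the two follow-up samples at day 4 and day 28.
- **Contacts.** Under Follow-up, staff phone or text the women about both questionnaires and control samples: "The phone calls or text-messages are app. made on day 3–5, day 9–11 and day 28–30, respectively". The text does not say whether a symptom score is noted.
- **Analysis sets.** Under Power, sample size and analysis, Definitions, ITT is everyone included, PP is "all the patients that follow-up with clinical and bacteriological data", and NTT is a subset of PP.
- **Planned loss.** Power analyze: "With an estimated fall-out rate of app. 30" per cent, with 113 (NTT), 161 (PP) and 230 (ITT) per group.

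**The concern.** The day-4 score depends on urine delivery in two ways.

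The first is a stated rule. PP asks for clinical and bacteriological follow-up data together, so a woman with a full diary and no control urine is removed from the clinical comparison. NTT is cut from PP, so it inherits the exclusion.

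The second is an inference. If the diary travels with the urine, a woman who sends no urine may well send no diary, and ITT then includes her without a day-4 score.

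The loss need not be random. Under Criteria for termination from the study, treatment failure ends participation, and Second medical consultation sends women with worsening or no relief back to the GP. A woman who fails before day 8–10 may leave before the sample that would carry her diary. The planning rates imply more failures in the 3-day arm (25% against 10%), so loss could depend on both arm and outcome. What is at stake is bias in the endpoint that the protocol puts first.

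**Working it through.** **Inputs.** From Power analyze: 90% v 75%, two-sided 0.05, power 0.80, fall-out about 30%, and 113/161/230 per group. The split of the fall-out by cause (no urine, no diary, withdrawal) is not given.

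**1. Reproduce the plan's figures.** Without continuity correction, with mean rate 0.825:

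n = [1.96·√(2·0.825·0.175) + 0.8416·√(0.90·0.10 + 0.75·0.25)]² / 0.15² = 99.5, so 100.

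With correction: (n/4)·[1 + √(1 + 4/(n·0.15))]² = 112.5, so 113, as stated. Then 113/0.7 = 161.4 (stated 161) and 161/0.7 = 230.0 (stated 230). The 30% is therefore applied twice, once between ITT and PP and once between PP and NTT.

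**2. Planned loss from ITT to PP.** 230 − 161 = 69 per arm, and 69/230 = 30%. This is the most that undelivered urine could account for within the planned loss. Women who drop out of PP with a diary but no urine are among the 69 and do have a clinical score, so the number unscored lies between 0 and 69.

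**3. Unscored women counted as not cured (assumed rule).** The protocol states no such rule. Take 90% and 75% as the cure rates among scored women, and let m5 and m3 be the unscored shares in the 5-day and 3-day arms. The difference is (1 − m5)·0.90 − (1 − m3)·0.75.
- m5 = m3 = 0.30: 63.0% − 52.5% = 10.5 points.
- m5 = 0.25, m3 = 0.35 (assumed): 67.5% − 48.75% = 18.75 points.
- m5 = 0.35, m3 = 0.25 (assumed): 58.5% − 56.25% = 2.25 points.

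**4. Extreme bounds on the ITT difference.** All unscored women are set to cured in one arm and not cured in the other.
- 30% unscored: 63.0 − (52.5 + 30) = −19.5, to (63.0 + 30) − 52.5 = +40.5 points.
- 15% unscored (half of the 69 scored after all): 76.5 − (63.75 + 15) = −2.25, to (76.5 + 15) − 63.75 = +27.75 points.
- None unscored: 15 points.

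**5. Power among scored women** at 90% v 75%, no continuity correction: 94.7% with 161 per arm, 97.6% with about 195, and 99.0% with 230. This applies to a comparison of scored women. A rule that counts the unscored as failures dilutes the effect itself, as in step 3.

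**The case against.** The sentence on submission describes logistics. It does not say that a diary without urine is refused. Staff chase questionnaires in their own right at day 9–11 and day 28–30, and a woman who misses the first control sample can still enclose the diary with the second. A reader might infer that no urine means no day-4 score, or that staff do not ask about symptoms at the contacts. The documents support neither: the first is only likely, and on the second a condensed article is merely silent.

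The figure of 69 could likewise be misread as the number of women without a clinical score. The fall-out rate is not split by cause, and the protocol lists other ways out of the study, including withdrawal and adverse effects. The unequal losses and the not-cured rule in the working are assumptions. They show how sensitive a result is to 30% missing scores, whatever the cause, and do not measure the effect of linked submission.

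It can also be said that missing-data handling belongs in the analysis plan, and that PP is reported beside ITT. That holds for the choice of imputation, which is not criticised here. It does not dispose of the point: the PP definition is fixed in the protocol article, and no analysis rule recovers a score that was never collected.

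Finally, a single contact score cannot serve time to cure, and women who stop returning material may not answer the phone. Both limits stand.

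**Conclusion.** The point holds in a limited form. It is certain from the text that the PP definition removes women with complete clinical data but no urine from a clinical analysis that needs none. It is likely, not certain, that the single described return route also costs ITT some day-4 scores. The size cannot be fixed from the documents: at most 69 per arm of the planned loss, possibly far fewer. At that upper bound, and under the assumed rules, the 15-point difference could appear as anything from 2.25 to 18.75 points, while power among scored women stays near 95%. The issue is possible bias, and its direction cannot be determined. To conclude that unscored women largely determine the ITT result would go beyond the evidence, because it takes the whole 30% as missing clinical scores. The change is worth making because it is cheap and protects the endpoint of main interest.

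**What to change.** 1. **Power, sample size and analysis, Definitions.** Define PP per endpoint: clinical data only for the clinical endpoint, urine data for the bacteriological one.
2. **Questionnaires.** State that the diary is returned whether or not urine is delivered.
3. **Follow-up.** Set the existing day 3–5 contact on day 4 and record the three symptom scores (dysuria, urgency, frequency; 0–3 each). Use them for the day-4 proportion only, and only when the diary is missing, with a sensitivity analysis on diary scores alone. Use the day 9–11 contact to retrieve the diary, not to score day 4 by recall.
4. **Microbiological diagnostics and the Outcomes paragraph of the Discussion.** Reconcile the date of the first control urine (day 8–10 or day 4), since it also governs when the diary comes back.

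Cost: a small amendment and three short questions at a contact already made, with no new visit. The drawbacks are a second mode of recording (phone or text) for some women and PP sets of different size for the two endpoints. Time to cure still depends on the diary.

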#### Microbiological diagnostics

One pre-treatment urine sample (day 0) with optional urine-dipstick, and two control urine samples (day 8–10 and day 28–30, respectively) will be sampled from the patient. The three urine samples will be sent to the DCM, Hvidovre University Hospital, Denmark, for examination of the presence and count of uropathogenic bacteria. In presence of significant bacteriuria (i.e. ≥10^3^ bacteria/ml [*E. coli*] / ≥10^4^ bacteria/ml [other uropathogenic bacteria]) the isolates will also be examined for resistance mechanisms and patterns, minimal inhibitory concentration (MIC) to mecillinam (i.e. by E test, AB Biodisk, bioMe’rieux, Marcy-l’E’ toile, France) and determining the bacterial specimen (i.e. MALDI-TOF, Brukner, Germany). All urine samples will processed according to laboratory routine and susceptibility tested according to EUCAST guidelines [18]. During the study all significant uropathogenic isolates will be stored at minus 80 °C. At the end of the study these isolates will be genetically examined to determine their more specific identity/type, i.e. so we can evaluate if the potential relapse is either a true relapse or a reinfection (i.e. the same or different type of bacterial specimen).

